### Evaluation sites

This evaluation will take place in five regions across England: West (Bristol), North East and North Cumbria, West Midlands, Yorkshire and Humber and Greater Manchester. As of 2021, the average smoking prevalence among adults in England aged 18 and over is 13%.^8^ All regions in the evaluation have smoking rates higher than those of the national average: Bristol at 16%, the North East at 15%, West Midlands at 14%, Yorkshire and Humber at 14% and Manchester at 17%.^8^ As of 2022, the average smoking prevalence at the time of delivery in England was 8.8%. Four regions had higher smoking prevalence than the national average: North East at 12.5%, West Midlands at 11.4%, Yorkshire and Humber at 11.6% and Manchester at 9.2%. However, Bristol was slightly lower at 8.4%. Regarding mental health, as of 2022, smoking prevalence among adults with a long-term mental health condition in England was 25.2%.^8^ Four regions were higher than the national average: West Midlands at 25.5%, Manchester at 31.0%, Bristol at 30.4% and Yorkshire and Humber at 27.5%; however, North East of England was lower with 23.5%.^8^

## Methods and analysis

A mixed-method evaluation of effectiveness and implementation will be undertaken to explore the impact of the service on health and care outcomes.^9^ This hybrid approach will integrate analysis of qualitative interviews, document analysis and surveys with analysis of routinely collected patient data and health economic data.^9^

We developed an initial logic model based on the NHS-funded tobacco dependence implementation plan across the three settings (table 1), and additional documentation provided by the Office for Health Improvement and Disparities (e.g., detailed treatment pathways for each setting, via email), illustrated in table 3 below. This representation of pathways from implementation strategies and mechanisms to an intervention’s outcomes will be amended using evidence generated from work package (WP) 1, key informant interviews and document analysis. The logic model presents the anticipated outcomes of implementing this intervention in the short, medium, and long terms; however, not all outcomes will be assessed as part of this evaluation. Details on outcomes relevant to this evaluation are reported in their respective WPs (where applicable).

**Table 3 T3:** Initial logic model for the implementation of the NHS-funded tobacco dependence services

Inputs	Processes	Outputs	Outcomes and impacts		
			Short term	Medium term	Long term
Funding to deliver the tobacco dependency service (TDS) including the provision for further staff Staff needed to deliver the intervention within the TDS The time needed to understand the process changes (staff training, technology changes, etc) Technology (record keeping, medication dispensing, referrals, communication with General Practitioners (GPs) and local stop smoking services (SSS)) Long Term Plan (LTP), National Policy and Trust Policy Regional TDS protocol/implementation plans Trust protocol development Communication pathways between the admitting team, TDS team, GPs and SSS Creation of training packages	Staff training in very brief advice (VBA) and nicotine replacement therapy (NRT) Recruitment of additional staff Creation of a TDS team of specialised staff (and its fitting in the wider hospital teams) Stakeholders and staff involvement in protocol/trust policy development and delivery Implementation and enforcement of protocols Technology adapted to record new data collected regarding smoking status Medication protocols for prescribing (NRT) and tobacco dependency (TD) medications Space for recording NRT preferences and prescription Kardex (or online system, that is, ePMA) Documentation of TD medication/NRT administration Creation of a/multiple referral scheme(s)/pathway for admitting staff/TDS staff/community support post-discharge Communication channels between staff/TDS/community/GP	Patients screened for smoking status in acute/maternity/mental health Delivery of intervention (dependent on pathway) VBA provided and NRT prescribed to those identified as smokers Tobacco dependent advisor (TDA) to provide a comprehensive assessment of identified smokers needs TDA to provide an assessment, CO testing, NRT options and behavioural advice Discharge with ongoing support or onwards referral in the community for inpatient pathway/and adapted for MH pathway. Maternity will provide ongoing support Provide follow-up as protocol dictates	Increase in smoking status recording Increase in NRT prescribing Increase in quit date set Increase in CO recording (will be dependent on if recording systems allow for that in inpatient, currently data metrics from NHS do not have requirement for this)	Continuation of support in the community Reduced length of hospital stay Increase the number of quitters being supported in the community & referrals to community services on discharge Better clinical management of illness in hospital. Reduction in re-admission Bed days saved Reduction in smoking on hospital sites Reduction in NHS staff smoking Increase in partners attempting to quit during pregnancy More smoke-free homes during pregnancy Hospital sites being smoke free	Long term quit (with/out community support) Reduced smoking-related admissions Reduction in smoking-related illness and deaths Reduction in years of disability Increase in quality of years of life Reduction in smoking population Reduction in NHS staff smoking Change in staff attitude towards smoking, not a lifestyle choice but medical condition
**Unintended consequences/dark logic model**^33^ Risk of widening inequalities and/or barriers to participation for marginalised groups. Risk of increased tension between primary and secondary care. Increased time pressures and paperwork for staff. Potential pressure on Local Authority Stop Smoking Services pharmacotherapy budgets.					

### Programme setup—pre-evaluation activities (months 1–12)

The first year of funding will be used to appoint researchers across the evaluation regions, obtain the relevant ethical approvals and data-sharing agreements and complete procedures for setting up participating NHS Trusts.

### WP 1: key informant interviews and document analysis (months 13–24)

#### Design

This qualitative WP aims to characterise the implementation context, using key informant interviews and document analysis. It will describe currently available smoking cessation services, provisions and structures in each of the evaluation regions, as well as NHS TDS implementation plans. Data will facilitate the refinement of the logic model described in the preceding section.

#### Sampling and recruitment

Participants will be purposively selected from all three settings (table 1) based on their relevant knowledge and role to ensure that the most relevant informants are interviewed. This will include front-line healthcare professionals (e.g., doctors, nurses, specialist smoking cessation staff) from all three settings, and service commissioners and managers responsible for tailoring/leading the implementation of the service. Participants will be recruited through key contacts in each of the geographical regions (via email) combined with a snowballing approach.

### Data collection

#### Interviews

We will conduct semi-structured interviews across the five evaluation regions. Interviews will be conducted by members of the research team local to each region, either face-to-face (in line with COVID-19 restrictions), telephone or secure videoconferencing platform (e.g., Teams/Zoom). Interviewers will be experienced researchers, from related disciplinary backgrounds (eg, public health, behavioural science), with no prior relationship with or knowledge of participants and their backgrounds. A bespoke topic guide (online supplemental file 1) informed by existing literature and discussions with the research team^10^,^13^ has been pilot-tested and will be used to guide conversation. All interviews will be recorded and transcribed verbatim. Transcribed data will be anonymised, with participants’ names replaced with unique participant IDs. Digital recordings and digital transcripts will be stored on a secure server. Data collection and recruitment will be guided by data saturation and information power, as aligned with the evaluation aims and proposed methods (including application of theory and analytical method).^14 15^

#### Document analysis

We will source relevant documents including, but not limited to hospital policies, implementation plans, and protocols concerning the NHS TDS from the five evaluation regions (eg, through Smoke Free NHS Leads, Treating Tobacco Dependency Taskforces within Integrated Care Systems). National-level policy is publicly available online.

#### Analysis

Interview and documentary data will be managed using NVivo software^16^ and will be analysed thematically using established methods by members of the research team.^17^ Interview data analysis will be inductive, that is, data-driven, following a six-phase iterative process of coding data and theme generation. Documentary data will be coded using the Template for Intervention Description and Replication (TIDieR) framework, comprised of 12 items that will allow us to detail the rationale and procedures for intervention delivery and implementation settings.^18^ Data analysis will follow a six-phase approach in line with Braun and Clarke’s Thematic Analysis.^17^

### WP 2: surveys and interviews with healthcare professionals and interviews with smoking individuals (months 25–48)

#### Design

This mixed-method WP aims to explore staff and smoker perceptions of NHS TDS implementation and receipt, respectively, using a longitudinal quantitative survey and semi-structured interviews. Specifically, it aims to investigate barriers and enablers to NHS TDS delivery, explore how staff attitudes regarding smoking changes over time and explore smokers’ experiences of being offered, or receiving, NHS TDS.

### Sampling and recruitment

#### Healthcare professionals

Healthcare professionals involved in the implementation of NHS TDS in acute hospital, maternity or mental health settings in any of the evaluation regions will be eligible to take part. We define involvement as healthcare professionals as those who are expected to or have started to deliver NHS TDS in the above-mentioned settings (table 1). We will use a combination of convenience and snowball sampling techniques to recruit participants.

#### Smokers

Adults (aged 18 and over) who are identified as smokers in acute hospital, maternity or mental health settings and offered the service in any of the evaluation regions will be eligible to participate in interviews. Eligible participants will be identified by a healthcare professional and will seek consent from them to be contacted by the research team. We aim to interview a range of individuals across implementation settings and evaluation sites, for example, those who have been offered and engaged with the service; offered and declined the service and offered and engaged with the service then subsequently withdrawn. Participants will also be purposively selected based on demographic characteristics such as gender and ethnicity to capture a diverse range of perspectives on the service.

### Data collection

#### WP 2a—survey

An online survey using two validated tools—using the NOrmalization MeAsure Development (NoMAD) questionnaire,^18^ and the Capabilities, Opportunities, Motivations and Behaviour Model (COM-B) questionnaire^19^—will be sent via email to healthcare professionals at two time points. The first survey will be circulated as close as possible to the beginning of the implementation period, with the second survey circulated 6 months after the first. The NoMAD questionnaire is useful for understanding how interventions are routinised into practice, and the COM-B questionnaire is useful for understanding barriers and enablers to enacting behaviours (i.e., delivering NHS TDS). Participation is voluntary and participants will be recruited by email through their service managers/leads. Invitation emails will include a Participant Information Sheet and a link to participate in the survey. Within the survey, there is the opportunity to detail reasons for non-participation, should they choose to decline.

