**Methods and analysis:**

This is a national evaluation across five regions in England (i.e., South West, West Midlands, Greater Manchester, North East and North Cumbria, Yorkshire and Humber) including 11 NHS Foundation Trusts. It is funded from September 2021 to September 2025. Evaluation settings are acute hospital, maternity and inpatient mental health.

Work package (WP) 1 involves qualitative key informant interviews to characterise the policy implementation context. WP 2 involves an online survey to assess the routinisation of the service in practice and staff attitudes regarding tobacco dependence, plus in-depth interviews with relevant practitioners to explore survey findings and interviews with smokers to investigate its usefulness and impact. WP 3 involves descriptive statistical analysis of routinely collected data to assess service uptake and impact on health and care outcomes (e.g., smoking status). WP 4 involves an economic analysis of routinely collected data to determine the financial impact of the service. Qualitative data (WP 1, WP 2) will be analysed using Thematic Analysis and Framework Analysis, respectively. WP 2 survey data will be analysed using descriptive statistics.

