### Evaluation aims and objectives

The specific objectives for each study component are summarised in table 2. Implementation of the service (i.e., when the service was set up) nationally was set up to begin between in 2021/2022. Trusts participating in this evaluation started service implementation between February 2022 and November 2022, following challenges to service and data collection setup across the country. These studies are complementary to the national evaluation undertaken by NHS England (https://digital.nhs.uk/data-and-information/publications/statistical/statistics-on-nhs-stop-smoking-services-in-england).

**Table 2 T2:** Evaluation objectives and study components

Evaluation objective	Study components
To describe the implementation context, including practices, services and structures of pre-policy implementation	Work package (WP) 1: Key informant interviews and document analysis
To explore system-wide implementers’ (ie, front-line staff, managers or service leads, service commissioners) perceptions and experiences of service implementation	WP 2a: Survey of healthcare professionalsWP 2b: Interviews with healthcare professionals
To explore smokers’ perceptions of service implementation	WP 2c: Interviews with smokers offered the NHS-funded tobacco dependence services (NHS TDS)
To determine the level of participation in the NHS TDS	WP 3: Analysis of routinely collected patient data (effectiveness and process analysis)
To estimate service effectiveness as the change in number of smokers who have undertaken an intervention and self-reported and/or have a carbon monoxide (CO) confirmed 28-day quit	WP 3: Analysis of routinely collected patient data (effectiveness and process analysis)
To estimate the cost-effectiveness of the service per additional quit	WP 4: Health economic analysis

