#### WP 2b—interviews with healthcare professionals

Interviews with healthcare professionals approximately 12 months after intervention implementation. We anticipate 30 one-off semi-structured interviews either face-to-face, phone or secure videoconferencing platform (e.g., MSTeams/Zoom). A bespoke topic guide (online supplemental file 2) informed by NPT^20 21^ will be used to explore healthcare professionals’ experiences of implementing the NHS TDS. Interviews will last no longer than 1 hour and will be audio-recorded or video-recorded and transcribed verbatim by a professional transcription company.

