#### Analysis: survey

Data will be managed using STATA.^23^ Questionnaires will be analysed descriptively, using absolute (n) and relative frequencies, means and SD as appropriate to the level of data, and 95% CI.^24^ Mean scores for each of the four NPT constructs and the six COM-B constructs will be calculated.^25^ Higher positive scores on NPT constructs are suggestive of greater potential for the NHS TDS to ‘normalise’ or become routinised.

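### The WP 2 window opens 10 to 19 months after Trusts began the service, which contradicts the stated timing of the staff survey and, for many possible start dates, of the staff interviews

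*Protocol article*

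**What the plan says.** Four statements in the protocol article bear on this.

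- **Calendar.** The abstract says of the evaluation: "It is funded from September 2021 to September 2025". The section on programme setup equates months 1–12 with the first year of funding.
- **Service start.** Under Evaluation aims and objectives: "Trusts participating in this evaluation started service implementation between February 2022 and November 2022". The same section explains implementation as the setting up of the service.
- **WP 2 window.** The WP 2 heading covers the staff surveys, the staff interviews and "interviews with smoking individuals (months 25–48").
- **Timing inside WP 2.** For the survey (WP 2a): "The first survey will be circulated as close as possible to the beginning of the implementation period", with a second wave 6 months after the first. For WP 2b: "Interviews with healthcare professionals approximately 12 months after intervention implementation".

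The WP 2 design calls the survey longitudinal and gives as one aim to "explore how staff attitudes regarding smoking changes over time". The survey analysis is descriptive (frequencies, means, SD, 95% CI) and adds: "Mean scores for each of the four NPT constructs and the six COM-B constructs will be calculated".

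**The concern.** A reader who sees that wave 1 goes out near the beginning of implementation, with wave 2 half a year later, will take the pair as showing how staff views and routinisation moved while the service was bedding in. That is when NoMAD and COM-B scores might be expected to shift. If the survey runs in the window given for WP 2, every Trust has been delivering for most of a year or longer before wave 1. A flat result between waves could then mean that the service had already settled, and a high wave 1 score could not be read as an early one.

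The staff interviews have the same difficulty: the 12-month point that the article fixes for them lies before WP 2 opens for a large part of the range of start dates.

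**Working it through.** **Inputs.** Month 1 = September 2021 (abstract; programme setup section). Trust start = February to November 2022 (Evaluation aims and objectives). WP 2 = months 25–48 (WP 2 heading). Gap between waves = 6 months (WP 2a). Interviews at about 12 months (WP 2b).

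**Check of the month count.** With month 1 = September 2021, month 12 is August 2022, month 25 is September 2023 and month 48 is August 2025. This fits the stated end of funding in September 2025.

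**Formulas.** Project month of start, s = calendar months from September 2021, plus 1. Earliest wave 1 = 25 − s months after start. Earliest wave 2 = 25 − s + 6. Interview point = project month s + 12.

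| Trust start | s | Earliest wave 1 (months after start) | Earliest wave 2 (months after start) | 12-month interview point |
|---|---|---|---|---|
| February 2022 | 6 | 25 − 6 = 19 | 25 | month 18, before WP 2 |
| August 2022 | 12 | 25 − 12 = 13 | 19 | month 24, before WP 2 |
| September 2022 | 13 | 25 − 13 = 12 | 18 | month 25, WP 2 opens |
| November 2022 | 15 | 25 − 15 = 10 | 16 | month 27, inside WP 2 |

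So wave 1 is at least 10 to 19 months after start and wave 2 at least 16 to 25. The 12-month interview point spans months 18 to 27 and precedes the window for starts from February to August 2022.

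**Sensitivity to the anchor.** Counting from October 2021 widens the wave 1 gap to 11–20 months. For month 25 to coincide with the Trusts' start, month 1 would have to lie between February and November 2020, before funding began. No reasonable reading of the month numbers closes the gap.

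**Wave against implementation time.** Start dates spread over 15 − 6 = 9 months, more than the 6 months between waves. If each wave goes to all Trusts on one date, and that date is the earliest allowed, the last Trust at wave 2 (16 months) is earlier in its implementation than the first Trust was at wave 1 (19 months). Under common dates, wave number therefore does not order Trusts by time since start.

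**The case against.** The best defence is that the wording is soft and that the month headings are planning windows, which do not show when the survey was sent. Both points are fair, but they do not remove the conflict. A promise to be as close as possible cannot absorb a gap of at least 10 months at every Trust. If the survey went out earlier, the WP 2 window is wrong; if it did not, the survey timing is wrong. WP 3 has the same window yet uses records from December 2022, but records can be extracted later, whereas a survey cannot be back-dated.

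It is also fair that the stated aim is change over time, not change since go-live, and that two waves can describe a 6-month shift in mean scores, though convenience and snowball recruitment lets the respondents differ between waves. It would be too strong to say that the survey cannot show change.

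The article does not support these further inferences:

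- **That responses are not linked between waves.** It is silent on linkage and calls the survey longitudinal; identifiers and paired analysis may sit in the full protocol. A figure for the precision lost would also need an assumed within-person correlation and overlap of respondents.
- **That wave 1 is presented as a baseline.** The survey section does not use that term.
- **That all Trusts are surveyed on the same dates.** This is not stated, and circulation could be staggered by Trust. The comparison of 16 with 19 months holds only under common dates.
- **That WP 1, opening in month 13, cannot meet its objective on "practices, services and structures of pre-policy implementation".** WP 1 already combines informant interviews with policy and planning documents, which can describe earlier practice.

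**Conclusion.** The contradiction is real and follows from the article's own dates. Within the stated window, wave 1 is no earlier than 10 to 19 months after go-live and wave 2 no earlier than 16 to 25 months. The 12-month interviews cannot be on time inside WP 2 for Trusts that started from February to August 2022, which is 7 of the 10 possible start months. The number of Trusts concerned is unknown, because the article gives no distribution of start dates.

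The conclusion assumes that month 1 is September 2021 and that WP 2 data collection keeps to its heading. On those terms both surveys describe an established service and support only a statement about change between the two waves, not change from early implementation. The added point, that wave does not index implementation time across Trusts, depends on common circulation dates. This is a matter of dating and interpretation and does not invalidate the survey.

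**What to change.** 1. Reconcile the WP 2 window with the Trust start dates, the WP 2a survey timing and the WP 2b interview timing.
2. Replace the references to the beginning of implementation and to about 12 months with the actual months since each Trust's go-live, for each survey wave and for the interviews.
3. Report NoMAD and COM-B construct scores by months since Trust go-live, beside the wave means.
4. Limit the change-over-time conclusion to the interval that the two waves cover.
5. If responses are linked across waves, also report paired change with 95% CI among staff who answered both.

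The cost is one date variable per Trust, already known to the team, and some rewording. Items 1 to 4 can still be done at analysis and reporting if the waves have already gone out. The drawbacks are a less favourable description of wave 1 and, for item 5, that staff who answered both waves are a subset of respondents and may differ from the rest.
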